### Interventions

#### Interventions common to both arms

Pre-procedure management will be identical for participants in the two groups and will be conducted at our interventional suites at the study sites. This includes obtaining peripheral intravenous access and application of routine electrocardiogram, non-invasive blood pressure, and pulse oximeter monitors. Oxygen by nasal prongs or mask and light sedation with midazolam and or fentanyl at the Anesthesiologist’s discretion will be provided. The RFN procedure will be performed at the same levels as identified by the diagnostic medial branch nerve blocks.

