The following are the *secondary outcomes*:Pain intensity: The between-group difference in mean NRS for pain intensity scores at 1, 6, and 12 months after the interventions.Incidence of analgesic response: The between-group difference in the proportion of patients with a positive analgesic response (defined as 50% or greater reduction in the NRS score for neck pain as compared to baseline) at 1, 6, and 12 months after the interventions.Neck pain-related disability: The between-group difference in the proportion of patients with a 10% or greater reduction in the Neck Disability Index (NDI) score at 1, 3, 6, and 12 months after the interventions.Participant-assessed improvement: The between-group difference in the proportion of participants reporting some or much improvement on the Patients’ Global Impression of Change (PGIC) scale at 1, 3, 6, and 12 months after the interventions.Quality of sleep and life: The between-group difference in the mean Pittsburgh Sleep Quality Index (PSQI) scores and EuroQol (EQ-5D-5L) scores at 1, 3, 6, and 12 months after the interventions. Sleep health will be assessed using PSQI, and actigraphy-measured variables respectively, including sleep duration, sleep quality, daytime sleepiness, sleep timing, and wakefulness after sleep onset.Procedure-related outcomes: The between-group difference in the duration of procedure, discomfort, radiation dose, and cost of the procedures.Actigraphy-collected physical activity and sleep: The between-group difference in the average physical activity and sleep duration as measured by wrist-worn actigraphy over 1 week prior to the procedure and 1 week prior to the 1-month follow-up after the interventions.Adverse effects of the interventions: The between-group difference in the incidence of peri-procedural complications and post-procedural adverse effects at 1, 3, 6, and 12 months after the interventions.Analgesic requirements: The between-group difference in opioid requirements as measured by daily oral morphine equivalents in milligrams averaged over the 1 week prior to the 1, 3, 6, and 12 months follow-ups after the interventions.The patient assumption of the group they were assigned to at 3-month follow-up after the study interventions

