### Sample size

The sample size was calculated using the Statistical Package for the Social Sciences (SPSS, IBM SPSS Statistics) software. A sample size of 72 participants (36 in each treatment group) will provide 80% power to detect a difference (inferiority margin), at 3 months after the intervention, in the mean NRS pain intensity scores (0–10 scale) between the two treatment groups being less than or equal to 1 point, given a standard deviation (SD) of 1.7 at the 0.05 significance level (alpha) using a two-sided two independent sample *t*-test. To satisfy both the non-inferiority and superiority hypothesis, we plan to recruit a total of 80 participants to account for a presumed 10% dropout rate. The sample size calculations and the assumptions underlying it are based on data published on RFN of nerves supplying other axial joints (lumbar facets, sacroiliac) for the relief of spinal pain [12, 13]. The chosen non-inferiority margin of less than or equal to 1 point (10%) is reasonable because a minimal clinically important difference in pain scores for a treatment to be considered efficacious is 2 points or 30% [14]. A non-inferiority study is justified to compare the end-on and parallel RFN lesions because similar efficacy is expected but there may be a lower incidence of adverse effects (e.g., patient discomfort) and better resource utilization (e.g., faster procedure time, lower radiation dose) with the end-on RFN technique.

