### Assignment of interventions

#### Randomization, sequence generation, and allocation concealment

Upon participant enrollment, patients will be randomized to one of two arms, with a 1:1 allocation. The randomization sequence will be computer-generated by a member of the research team. An independent research coordinator will handle the treatment allocation process. This coordinator will ensure allocation concealment by using sequentially numbered, sealed opaque envelopes. The allocation sequence will be provided to an attending staff pain medicine physician.

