### Statistical methods

A statistician will be consulted to assist in data analysis and interpretation. Descriptive information for the sample’s study measures will include frequency distributions or proportions for categorical variables and means (standard deviations) or medians (interquartile ranges) (if non-normally distributed) for the continuous variables. To compare data between the two groups, categorical outcomes will be analyzed with the chi-square test and continuous variables will be analyzed with independent *t*-tests (or Wilcoxon rank sum test, as appropriate). A two-sided *p*-value of < 0.05 will be considered statistically significant. Both intention-to-treat (based on study arm allocation) and per-protocol (based on the participants who adhered to the study protocol and provided data at study outcome time points) analysis will be performed and reported.

Correlation between reduction in pain and improvement in function will be evaluated with a longitudinal model of changes from baseline to 3-month, 6-month, and 12-month follow-ups. An intention-to-treat strategy will be used for all analyses. Differences in treatment effects and 95% confidence intervals for pain and secondary outcome scores will be calculated using chi-square and odds ratios for dichotomous variables, and ANOVA (with *t*-tests for pairwise comparisons) and Mann–Whitney for continuous variables, as indicated. A set of logistic regression models for categorical outcome at 3 months will be created using variables hypothesized to have an effect on treatment (gender, intensity of pain, nature of injury), as well as those found to have a *p*-value less than 0.20 in univariate analysis. A secondary analyses based on data from participants who undergo unilateral versus bilateral RFN with each of the two study treatments is also planned. Missing data will be imputed using the “last observation carried forward” approach if at least 80% of the outcome data is available for the participant. All analyses will be performed using the SPSS program.

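### Procedure duration, radiation, cost and discomfort are compared with unadjusted tests although the extent of treatment varies and is known before allocation; this costs precision, not validity

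*Protocol article*

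**What the plan says.** - **Who is treated, and how much.** Table 1 requires a positive response to two diagnostic blocks but limits neither sides nor levels. Under Study intervention and active comparator groups, the treating physician chooses the block levels case by case. Under Interventions common to both arms: "The RFN procedure will be performed at the same levels as identified by the diagnostic medial branch nerve blocks".
- **Allocation.** "Upon participant enrollment, patients will be randomized to one of two arms, with a 1:1 allocation". Trial design places randomisation on the day of the procedure. Neither section names a stratification factor.
- **Procedure outcomes.** Among the secondary outcomes: "The between-group difference in the duration of procedure, discomfort, radiation dose, and cost of the procedures". Table 2 gives the units as minutes, Canadian dollars, a 0-10 score and mSv, with no denominator such as nerves or sides.
- **Analysis.** Statistical methods assigns continuous outcomes to independent t-tests or the rank-sum test, and later to ANOVA or Mann-Whitney, all without covariates. The only covariate models are logistic models for the 3-month categorical outcome, and the variables named there are gender, pain intensity and nature of injury.
- **Laterality.** It appears only as a separate item: "A secondary analyses based on data from participants who undergo unilateral versus bilateral RFN with each of the two study treatments is also planned". No outcome, contrast or method is given.
- **Role of these outcomes.** The Sample size section justifies the non-inferiority design partly by expected gains in discomfort, procedure time and radiation dose.

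**The concern.** Treating both sides, or more levels, should take longer and need more imaging than treating one side at one level. A per-procedure total then mixes the effect of technique with the spread in how much was treated. The plan regards laterality as important enough for its own analysis but does not use it where it would help most, in the between-arm comparison of procedure outcomes.

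If end-on lesioning proves non-inferior on pain, the case for adopting it rests largely on these outcomes. An imprecise comparison could miss a real saving in time or radiation. A chance excess of bilateral cases in one arm would also move the estimate, with no correction planned.

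**Working it through.** **1. Number per arm.** "A sample size of 72 participants (36 in each treatment group) will provide 80% power", and "we plan to recruit a total of 80 participants to account for a presumed 10% dropout rate". With margin 1 and SD 1.7, the normal formula n = 2(z₁₋α + z₀.₈)²·SD²/margin² gives 2 × (1.645 + 0.842)² × 2.89 = 35.7, so 36 per arm at one-sided 0.05, and 72/0.9 = 80. The printed two-sided 0.05 would give 45.4, so 46 per arm. That is a separate matter; only the 36 per arm is used below.

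**2. Is extent a baseline variable?** Positive blocks are an entry criterion, treated levels follow the blocks, and randomisation comes later. The text speaks of levels; that the side is also settled by then is a natural inference. Extent is therefore independent of arm in expectation. A simulation of the unadjusted t-test (36 per arm, bilateral time twice unilateral, 30% or 50% bilateral) gave type I error of 0.049 and 0.051 and a mean difference of about zero. There is no systematic bias.

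**3. Precision.** All inputs in this step are assumptions: bilateral share q = 0.3 to 0.5, means 30 and 60 min, within-type SD 8 min.

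Raw variance = 8² + q(1−q) × 30². Half-width = t(0.975, 70) × SD × √(2/36) = 1.994 × SD × 0.2357.

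| Analysis | SD (min) | 95% half-width (min) |
|---|---|---|
| Raw, q = 0.3 | √253 = 15.9 | 7.5 |
| Raw, q = 0.5 | √289 = 17.0 | 8.0 |
| Adjusted for laterality | 8 | 3.8 |

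Fitting the covariate costs one degree of freedom and leaves the adjusted figure at about 3.8.

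**4. Sensitivity to the time gap** (q = 0.4, SD 8):

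| Bilateral time | Raw SD (min) | Raw SD / 8 |
|---|---|---|
| 60 min (2×) | √(64 + 0.24 × 900) = 16.7 | 2.1 |
| 45 min (1.5×) | √(64 + 0.24 × 225) = 10.9 | 1.36 |
| 36 min (1.2×) | √(64 + 0.24 × 36) = 8.5 | 1.07 |

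A second set of assumptions keeps the doubling but lets the per-side coefficient of variation run from 0.2 to 0.4. Laterality then explains 38% to 81% of the variance of duration. An effect that the adjusted analysis detects with 80% power is detected by the raw test with about 23% to 59%.

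**5. Chance imbalance.** With two independent binomials (36, q) and q = 0.3 to 0.5, the bilateral share differs by at least 10 percentage points with probability 0.37 to 0.41, and by at least 15 with probability 0.16 to 0.19. A 15-point imbalance shifts mean duration by 0.15 × 30 = 4.5 min. The raw standard error is 15.9 × 0.2357 = 3.7 to 17.0 × 0.2357 = 4.0 min, so the shift is 1.1 to 1.2 standard errors and lies inside the raw interval. To reach the half-width alone, imbalance must be 7.5/30 to 8.0/30, about 25 to 27 points, which has probability 2% to 3%.

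**6. The laterality analysis.** At an even split there are 18 patients per cell. For a 1-point treatment-by-laterality interaction on the pain score with SD 1.7, SE = 1.7 × √(4/18) = 0.80 and power = Φ(1/0.80 − 1.96) ≈ 24%.

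**The case against.** The strongest reply has four parts.

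- **Randomisation already deals with extent.** This stands. A reader might infer that extent of treatment confounds the arm comparison, or that gains in time or radiation could be produced by case mix. The documents do not support that: extent precedes allocation, and the raw interval already allows for chance imbalance (step 5). The shift and the wider interval are one source of variation and must not be counted twice. The word confounding would fit only a comparison of unilateral with bilateral patients within an arm, which is not randomised.
- **The article may be condensed.** Also fair for stratification: an unprinted stratum cannot be excluded, and recruitment began in March 2023, so it is late to introduce one. It does not cover the analysis, because the article does state the tests and they are unadjusted.
- **The size is assumed.** True. No bilateral share, duration or SD is given, and nothing shows that cost or discomfort rises in proportion to the lesions made. The gain could be small (step 4).
- **Laterality is already examined.** Only in a separate secondary analysis. The screening rule of p below 0.20 belongs to the logistic models and does not reach the procedure outcomes.

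Any extra burden of a bilateral end-on procedure is part of that technique's real effect, which is a reason to keep the per-patient total as the main measure.

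**Conclusion.** The planned comparison of procedure outcomes is valid but less precise than it could be, and it leaves chance imbalance in extent of treatment uncorrected. The loss falls on outcomes that help to justify the non-inferiority design. Under the doubling assumption, the half-width for duration is about 7.5-8.0 min where an adjusted analysis would give 3.8 min. If bilateral treatment adds only a fifth to the time, the difference is negligible. These figures rest on assumed inputs and illustrate duration only.

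The point does not extend to the primary pain comparison. Nothing in the documents shows that laterality or number of nerves predicts the 3-month score, and that test is not invalidated. This is an inexpensive improvement in efficiency, not the correction of an error.

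**What to change.** Before unblinding, pre-specify for duration, radiation dose, cost and discomfort a linear model (ANCOVA) with treatment, laterality and number of nerves lesioned. Report the adjusted difference in the per-patient total with its 95% interval as the main result. Take sides and nerves from the diagnostic-block plan recorded before the envelope is opened, so that the covariates cannot be influenced by allocation. Robust standard errors are sensible, since longer procedures may also vary more.

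Define the unilateral/bilateral analysis as a treatment-by-laterality interaction, label it exploratory, and name the outcomes to which it applies.

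The cost is two covariates known before treatment and a few sentences in the analysis plan; no patients or visits are added. Stratifying the envelopes and adjusting the primary pain comparison for laterality are not required.

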### Outcomes

Patients will be assessed at baseline and 1, 3, 6, and 12 months after the study interventions. The assessment schedule and parameters are summarized in Table 2.

**Table 2 Tab2:** EndPaRL assessment schedule

**Outcome**	**Measure**	**Baseline**	**Immediate after procedure**	**1 month after procedure**	**3 months after procedure**	**6 months after procedure**	**12 months after procedure**
**Patient demographics**		**X**					
**Pain intensity**	NRS	**X**	**X**	**X**	**X**	**X**	**X**
**Neck disability**	NDI	**X**	**X**	**X**	**X**	**X**	**X**
**Global improvement**	PGIC			**X**	**X**	**X**	**X**
**Sleep quality**	PSQI	**X**		**X**	**X**	**X**	**X**
**Sleep duration**	In hours and minutes from actigraphy device	**X**		**X**			
**Physical functioning**	Time spent at different activity levels from actigraphy device^b^	**X**		**X**			
**Opioid intake**	Daily OME in mg	**X**		**X**	**X**	**X**	**X**
**Analgesics**	Name and dose	**X**		**X**	**X**	**X**	**X**
**Procedure** **(1) Duration** **(2) Cost** **(3) Discomfort** **(4) Radiation**	(1) In minute (2) In CAD (3) 0–10 (4) Dose in mSv		**X** **X** **X** **X**				
**Complications**	e.g., bleeding, hematoma		**X**				
**Adverse effects**				**X**	**X**	**X**	**X**
**Health-related quality of life**	EQ-5D-5L^a^	**X**		**X**	**X**	**X**	**X**

*CAD* Canadian dollars, *NRS* Numerical Rating Scale, *OME* Oral morphine equivalents

^a^EuroQol 5-level EQ-5D version (EQ-5D-5L); Neck Disability Index (NDI); Numerical Rating Scale (NRS); Patients’ Global Impression of Change (PGIC); Pittsburgh Sleep Quality Index (PSQI)

^b^Data on physical activity and sleep collected using participant-worn actigraphy devices (light/moderate/severe)

The following are the *primary outcomes*:The between-group difference in mean NRS for pain intensity scores at 3 months after the interventions.The between-group difference in the proportion of patients with a positive analgesic response (defined as 50% or greater reduction in the NRS score for neck pain as compared to baseline) at 3 months after the interventions.

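### The 80% condition on last observation carried forward leaves early dropouts without a 3-month value, so the primary analysis is in effect complete-case for them

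*Protocol article*

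**What the plan says.** Both primary outcomes sit at month 3. One is "The between-group difference in mean NRS for pain intensity scores at 3 months after the interventions"; the other is the proportion whose NRS has fallen by at least half from baseline. On timing, the Outcomes section says "Patients will be assessed at baseline and 1, 3, 6, and 12 months after the study interventions". Table 2 adds an NRS immediately after the procedure, which makes six scheduled NRS scores.

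Statistical methods compares the arms by t-test or Wilcoxon for continuous outcomes and by chi-square for categorical ones. It plans two analyses, "Both intention-to-treat (based on study arm allocation" being the first, with the per-protocol set "based on the participants who adhered to the study protocol and provided data at study outcome time points". It then states: "An intention-to-treat strategy will be used for all analyses". Missing values are filled by the LOCF "approach if at least 80% of the outcome data is available for the participant".

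The section does not define the denominator of the 80%, and it gives no handling below it. The Sample size section raises recruitment from 72 to 80 "to account for a presumed 10% dropout rate".

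**The concern.** An imputation rule matters most for people who leave before the primary time point. A condition requiring 80% of a participant's data seems likely to switch the rule off for exactly those people. The tests named cannot use a participant who has neither an observed nor an imputed 3-month score, so such a participant would leave the comparison even though it is labelled intention-to-treat.

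Two things are at stake. If dropout relates to poor pain relief and differs between arms, the estimated difference shifts relative to a 1-point non-inferiority margin. And the per-protocol set is itself defined by having provided data. If the intention-to-treat set loses the same early dropouts, comparing the two sets says little about their influence.

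**Working it through.** **Inputs.** Visit schedule and marked cells: Table 2. Dropout 10%, SD 1.7, margin 1 point, 36 per arm, 80 recruited: Sample size. Assumed here, because the document gives only overall dropout: the split between arms, and D, the number of NRS points by which dropouts are worse than completers.

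**Plan's own figures.** 72 / (1 − 0.10) = 80, as stated. The 36 per arm reproduces at one-sided 0.05: 2 × (1.645 + 0.842)² × 1.7² / 1² = 35.7. The two-sided 0.05 that the section states would need 46 per arm. That is a separate matter, but it is why both error levels appear below.

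**Step 1: who passes 80%?**

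| What is counted | Lost after the 1-month visit | Misses only month 3 |
|---|---|---|
| 4 follow-ups | 1/4 = 25% | 3/4 = 75% |
| Baseline + 4 follow-ups | 2/5 = 40% | 4/5 = 80% |
| All 6 NRS scores | 3/6 = 50% | 5/6 = 83% |
| Baseline, 1, 3 months | 2/3 = 67% | 2/3 = 67% |
| Baseline, immediate, 1, 3 months | 3/4 = 75% | 3/4 = 75% |
| All 50 marked cells of Table 2 | 26/50 = 52% | 42/50 = 84% |
| The 34 cells up to month 3 | 26/34 = 76% | 26/34 = 76% |

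The cells by visit are 9, 7, 10, 8, 8 and 8, from baseline to month 12. Loss before month 1 gives lower figures still (0% to 50%). Nobody lost before month 3 qualifies on any count.

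**Step 2: where does LOCF act at month 3?** Essentially only where someone misses month 3 but returns at both 6 and 12 months, on the three counts that reach 80% in the last column. The 1-month score is then carried forward and the later observed scores are ignored. Whether a 3-month value is imputed thus depends on data collected up to nine months later. If only the four follow-ups count, 80% of 4 means all 4, and LOCF never acts. If cells are counted, a blank NRS at an attended 3-month visit could also be filled.

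**Step 3: size of the loss.** 10% × 80 = 8 participants at most, if all presumed dropout falls before month 3.

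**Step 4: bias.** In each arm, mean of all randomised = mean of completers + dropout rate × D. So the bias in the difference (end-on minus parallel) = −(d_E − d_P) × D. Higher NRS is worse, so a negative bias flatters end-on.

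The table also gives the chance of wrongly declaring non-inferiority when the true difference among all randomised equals the 1-point margin. It comes from simulation with 40 per arm, SD 1.7 and 40,000 runs. Ranges run from D = 1 to D = 3.

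| Dropout, end-on vs parallel | Bias | False non-inferiority, one-sided 0.025 | One-sided 0.05 |
|---|---|---|---|
| 10% vs 10% | 0 | about 2.5% | about 5% |
| 15% vs 5% | −0.1 to −0.3 | 4.3% to 11.2% | 8.1% to 18.4% |
| 5% vs 15% | +0.1 to +0.3 | 1.4% to 0.4% | 2.9% to 0.9% |

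Each split gives 8 dropouts among 80; for example 15% of 40 + 5% of 40 = 6 + 2.

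**The case against.** The article does not say that participants below 80% are excluded, and a condensed article may leave their handling to an analysis plan. That is fair: exclusion is inferred from the tests named and the absence of another rule. The 80% condition itself, however, is fixed here.

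A reader might infer that the plan contradicts its own definition of intention-to-treat. It does not do so in words, because the section glosses the term as analysis by allocated arm, and allocation and missing outcomes are different questions. The conflict is one of effect.

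A reader might also infer a bias towards declaring non-inferiority. The document gives no dropout by arm. It expects possibly fewer adverse effects with end-on, which is no reason to presume more end-on dropout. The bias may be nil or go against end-on.

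Nor is LOCF confined to month 3: it can fill a single missed 6- or 12-month score. And narrowing of the confidence interval through single imputation would be negligible at month 3 if almost nobody is imputed.

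Other sections reduce the problem. Untreated participants are still assessed, withdrawn participants are asked to complete questionnaires if they agree, and the 3-month visit is in person. The step from 72 to 80 already covers the loss of power. These provisions may shrink the amount of missing data, but they leave the rule as it is.

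**Conclusion.** The point holds in this limited form. The 80% condition has no denominator and no stated handling below it. On every count drawn from Table 2 it gives early dropouts no 3-month value, so the primary comparison is in effect complete-case for them. As far as early dropout is concerned, the intention-to-treat and per-protocol sets nearly coincide, which weakens that cross-check. Where LOCF does act at month 3, it discards later observed scores.

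Up to 8 of 80 participants could be affected. The bias is nil with balanced, equally poor dropouts. It is 0.1 to 0.3 points (10% to 30% of the margin) in either direction under a 15%/5% split with dropouts 1 to 3 points worse. That split and severity are assumptions. The Table 2 arithmetic is firm; the direction of any bias is not known.

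**What to change.** Delete LOCF and the 80% condition. Estimate the 3-month NRS contrast from a mixed model for repeated measures with arm, visit, arm-by-visit interaction and baseline NRS, using all available scores from randomised participants by allocated arm.

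That model still omits anyone with no post-procedure score, so add these sensitivity analyses:

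- Multiple imputation covering all randomised participants, including those with no post-procedure score. Shift missing values worse in steps, in the end-on arm in particular, until the non-inferiority conclusion changes. Do not cap the shift at 1 point, since dropouts could plausibly be further off than that.
- For the responder outcome, count participants with missing 3-month response as non-responders. Read this beside the imputation result, because equal non-response in both arms also pulls the two proportions together.

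The cost is an analysis amendment, communicated as the Research ethics approval section requires (including to the ethics board and the registry) and made before unblinding, plus a little more analysis. No new data are needed.
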